# JUDGING CRITERIA or INTEREST VARIABLES

## Primary endpoint

The acceptability of the beta version of eMind will be assessed by the regularity of its use. We will define people who use eMind at least 4 times a week for 8 weeks as active users. Those using the application 1 to 3 times a week will be defined as occasional users, and those no longer using the application after 8 weeks will be defined as users who have given up using the application.

Usability will be assessed using the MARS-F usability scale (Mobile App Rating Scale, French version) after 8 weeks' use of the application. The MARS-F usability scale is made up of 23 items rated from 1 to 5, and explores four objective domains (engagement, functionality, aesthetics, information quality) leading to a score ranging from 0 to 95, and a subjective domain with 20 points. Usability is considered good if at least 75% of users award a MARS-F score of at least 85 out of 115.

After 8 weeks of use, focus groups will be set up with active users, occasional users and those who have given up using the application, to gather their perceptions and experiences with a view to collectively establishing recommendations for the evolution of the beta version of our application.

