## Follow-up / questionnaires

Participants will receive follow-up visits at 4 and 8 weeks of inclusion, as follows:

- Visit 2 (4 weeks from inclusion, university hospital addictology department at CHU Dijon Bourgogne)

- Collection of consumption schedule, measurement of CO

- Assessment of craving using VAS

- Assessment of withdrawal symptoms and NRT use

- Gather initial feedback on the regularity of use of the application in order to plan the formation of focus groups.

- Visit 3 (8 weeks from inclusion, University Hospital Addictology Department, CHU Dijon Bourgogne)

- Collection of consumption schedule, measurement of CO

- Assessment of craving using VAS

- Assessment of withdrawal symptoms and NRT use

- Assessment of eMind usability using the MARS scale

- Collect feedback on the regularity of application use.

The focus groups will be carried out between visit 3 and visit 4, in order to avoid any memory bias that might arise if they are carried out too far after the product has been used.

In order to obtain an overall assessment of feedback, expectations and the determinants of the application's acceptability and impact on participants, the following topics will be addressed during the focus groups:

- Knowledge/representations of eHealth tools: history, practice in what context, general opinion of eHealth tools

- Practical application and access to the tool: access to the tool (connection, handling, navigation, etc.), general appearance, flexibility and adaptability of use, suitability of the tool to the smoking cessation context

- Perceived impact on smoking behavior: changes in smoking habits, obstacles, helping factors, shortcomings.

- Improvements to the tool and addictology follow-up: additions/improvements to the tool/follow-up visits, application reminders, online tools for self-monitoring of consumption, access to healthcare professionals.

Visit 4 to 12 weeks after inclusion (M3). During this visit, the following tests will be performed:

- Collection of consumption schedule, measurement of CO

- Assessment of craving using VAS

- Assessment of withdrawal symptoms and NRT use

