## Technical description of measured parameters

- Tobacco consumption calendar, rated 0 = no consumption, 1 = 1 cigarette, etc., integrated into the eMind application: daily completion by the patient (with reminder notification).
- EVA Visual Analog Scale ("craving") rated from 1 to 10, integrated into the eMind application: weekly completion by the patient (with reminder notification).
- MARS-F Mobile Application Evaluation Scale composed of 23 items scored from 1 to 5 and exploring four objective domains (engagement, functionality, aesthetics, information quality) leading to a score between 0 and 95 and a 20-point subjective domain: collected at each visit by the investigator [15].
- Mindfulness practice calendar, integrated into the eMind application: daily completion by the patient (with reminder notification).

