## Description of the rules for discontinuing a person's participation in research

All those included will be followed until the end of the study, except for patients who have withdrawn their consent.

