# STATISTICAL ANALYSIS

## Analysis strategy

Analyses will be carried out on the frozen database resulting from the reconciliation of data collected on Cleanweb and Exolis.

Quantitative component

The MARS-F usability score will be calculated for each participant after the 8-week period of use. The score will be presented as a mean and standard deviation, accompanied by a 95% confidence interval.

The percentage of active, one-off and discontinued users will also be calculated, along with a 95% confidence interval calculated using the exact binomial method.

Secondary analyses will be descriptive and/or exploratory. Quantitative variables will be described in terms of means +/- standard deviations, medians and interquartile ranges.

Quality

The focus groups will be recorded and transcribed in full. The resulting corpus of qualitative data will then be processed by thematic analysis. Multidisciplinary (addictologist, public health researcher, epidemiologist) coding triangulation sessions will take place when the descriptive analysis framework is put together, and ultimately when the thematic tree (axial coding) is created.

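### The usability criterion is a proportion (at least 75% of users at 85/115 or more), but the planned MARS-F analysis gives only a mean, SD and CI, which do not determine that proportion

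*Protocol*

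**What the plan says.** Section 3.1 (Primary endpoint) makes usability at 8 weeks part of the primary endpoint and gives it a pass mark: "Usability is considered good if at least 75% of users award a MARS-F score of at least 85 out of 115". The synopsis repeats the rule under its evaluation criteria.

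Section 10.1 (Analysis strategy) first says "The MARS-F usability score will be calculated for each participant after the 8-week period of use", then "The score will be presented as a mean and standard deviation, accompanied by a 95% confidence interval". The only percentages it plans concern regularity of use: "The percentage of active, one-off and discontinued users will also be calculated, along with a 95% confidence interval calculated using the exact binomial method". The synopsis entry on statistical analysis has the same content. Section 10.3 adds that no test will be done and that the intervals are there to show precision.

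On who is scored and when:
- Section 6.4 lists "Assessment of eMind usability using the MARS scale" under Visit 3 (week 8) only.
- Section 6.7 describes MARS-F as "collected at each visit by the investigator".
- Section 6.9 states "All those included will be followed until the end of the study, except for patients who have withdrawn their consent".
- Section 3.1 keeps people who stop using the app as a class of users: "those no longer using the application after 8 weeks will be defined as users who have given up using the application".

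Section 4.2.1 expects some loss to follow-up among the 60 participants but gives no rate.

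**The concern.** The criterion asks what share of users reach a cut-off, while the analysis reports where the average lies. These are different quantities, and no part of the protocol plans to estimate the first or give it an interval. A report that followed section 10.1 to the letter would show a mean and CI beside a rule they do not answer. A mean a little above 85 would invite the conclusion that usability was good, when well under 75% of users might have reached 85.

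A second, smaller gap lies in the criterion itself. It refers to *users* without saying how a participant with no week-8 score is counted. The two descriptions of when MARS-F is collected differ, so it is unclear whether someone who misses Visit 3 would have any score. Since the verdict is a percentage against a fixed threshold, the choice of denominator can decide it.

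**Working it through.** **Inputs from the protocol.** Cut-off 85 of 115; required share 75%; N = 60. The maximum score reproduces: 19 objective items × 5 = 95, 4 subjective items × 5 = 20, and 95 + 20 = 115.

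**Assumptions (no figure in the protocol).** Score SD 8 to 15 with normality; loss before week 8 of 0% to 40%.

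**Step 1: what a mean says about the share.** Under normality, share at or above 85 = Φ((mean − 85)/SD). The mean needed for a 75% share = 85 + 0.674 × SD. The 95% CI half-width for the mean with 60 scores = 2.001 × SD/√60.

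| SD | Share ≥ 85 if mean is 88 | 95% CI for a mean of 88 | Mean needed for 75% |
|---|---|---|---|
| 8 | 64.6% | 85.9 to 90.1 | 90.4 |
| 10 | 61.8% | 85.4 to 90.6 | 91.7 |
| 12 | 59.9% | 84.9 to 91.1 | 93.1 |
| 15 | 57.9% | 84.1 to 91.9 | 95.1 |

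With SD 8 or 10, the whole interval for the mean lies above 85 while fewer than two thirds reach the cut-off. A mean of exactly 85 corresponds to 50%.

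**Step 2: the same point without normality.** Two constructed sets of 60 scores:
- 45 scores of 86 and 15 of 50: mean = (3870 + 750)/60 = 77; share = 45/60 = 75%. The criterion is met although the mean is below 85.
- 30 scores of 84 and 30 of 110: mean = (2520 + 3300)/60 = 97; share = 30/60 = 50%. The criterion fails although the mean is far above 85.

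The mean can therefore mislead in either direction.

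**Step 3: precision of the quantity that matters.** With all 60 scored, 75% is 45/60. The exact (Clopper-Pearson) 95% CI is 62.1% to 85.3%. This is the interval that the plan leaves out.

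**Step 4: the denominator.** For each assumed loss, take the smallest count that meets 75% among those scored and express it over all 60, counting missing scores as below 85.

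| Assumed loss | Among those scored | Same count over 60 |
|---|---|---|
| 10% | 41/54 = 75.9% | 68.3% |
| 20% | 36/48 = 75.0% (CI 60.4 to 86.4) | 60.0% (CI 46.5 to 72.4) |
| 25% | 34/45 = 75.6% (CI 60.5 to 87.1) | 56.7% (CI 43.2 to 69.4) |
| 30% | 32/42 = 76.2% | 53.3% |
| 40% | 27/36 = 75.0% | 45.0% |

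A bare pass among those scored becomes a fail over all 60 in every row. These are borderline cases by construction, and a result well above 75% among those scored could survive a modest loss.

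**The case against.** **The proportion can be counted anyway.** Section 10.1 has a score calculated for each participant and section 3.1 states the rule, so anyone holding the data can count those at or above 85. This stands against a claim that the trial could not apply its own criterion. It does not remove the mismatch: the protocol names its MARS-F summary, and that summary is not the quantity in the endpoint.

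**A statistical analysis plan may cover it.** One may exist and is not shown, and silence on missing-data handling alone would be no finding. The main point is not silence, however. Two sections of the protocol specify different quantities for one primary endpoint.

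**This is a pilot without a test.** It is single-centre, it serves to revise a beta version with help from focus groups, and nothing makes the later trial conditional on the 75% rule. That is fair and lowers the severity.

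**A stronger reading on the denominator.** A reader might infer that the criterion drops people who left before week 8 and is therefore biased upward. The protocol does not say so. Those who gave up remain a class of users, everyone except those who withdraw consent is followed, and the score is planned for each participant. Section 6.7 even has MARS-F collected at every visit. Someone who stops using the app but attends Visit 3 would be scored. Upward bias from non-attendance is plausible, but no figure in the protocol establishes it.

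**Counting missing as failure is debatable.** It mixes retention with usability, although regularity of use is measured separately as acceptability. With 45 of 60 scored, all 45 would have to reach 85 for the all-included figure to attain 75%. This argues against making it the sole rule and for showing both figures.

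**Conclusion.** The point holds as a mismatch between sections 3.1 and 10.1, repeated in the synopsis: the endpoint is judged on a proportion, and the planned analysis reports a mean. The gap is large enough to matter. Within the assumed SD range, a mean 3 points above the cut-off leaves the share reaching 85 some 10 to 17 percentage points short of 75%. The exact size depends on the assumed SD and normality; that a mean does not settle the criterion depends on neither, as the constructed examples show.

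On the denominator, the supported statement is limited. The criterion does not say how participants without a week-8 score count, and sections 6.4 and 6.7 conflict on when MARS-F is collected. The possible reversal (75.6% against 56.7%) rests on an illustrative 25% loss.

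This should be fixed. For an untested pilot with no progression rule tied to the threshold, it is not a fatal flaw.

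**What to change.** 1. In section 10.1 and the synopsis, name the proportion of participants with MARS-F of at least 85 as the primary usability estimate, with an exact binomial 95% CI, and set it against 75%. Keep the mean, SD and CI as supportive.
2. Report that proportion twice: among those with a week-8 score, and over all included participants with missing scores counted as not reaching 85. Define *users* in section 3.1 so that it is clear before any data are seen which figure the 75% rule applies to.
3. Reconcile sections 6.4 and 6.7 on whether MARS-F is collected at Visit 3 only or at each visit. If at each visit, say that the week-8 score is the one that counts.

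The cost is a few sentences and one or two extra table lines. Points 1 and 2 need no new data. The downside is that the all-included figure may be clearly less favourable than the figure among those scored, so the report should explain that it reflects retention as well as usability.

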## Secondary endpoints s

The evolution of tobacco consumption between inclusion and 4 weeks, 8 weeks and 12 weeks will be measured using an electronic consumption calendar implemented in our application. A CO test will be performed at inclusion, 4 weeks, 8 weeks and 12 weeks. Smoking abstinence will be defined as the absence of tobacco consumption for 7 days prior to the assessment visit. A recent consensus of experts has recommended the use of 7-day punctual abstinence as an endpoint, as it is less affected by recall bias and missing data than continuous abstinence (16).

Assessment of tobacco consumption at 6 months, during a telephone call.

Craving intensity will be measured at baseline, 4 weeks, 8 weeks and 12 weeks using a visual analog scale (VAS) implemented in the application.

The evolution of mindfulness practice between inclusion and 4 weeks, 8 weeks, 12 weeks will be measured using an electronic consumption calendar implemented in our application.

Evaluation of mindfulness practice at 6 months, during a telephone call.

Symptoms related to smoking cessation (cravings, difficulty concentrating, headaches, irritability, fatigue, hunger, constipation), use of nicotine replacement therapy (skin irritation, abdominal pain, hiccups, gastroesophageal reflux, sleep disorders, nausea, diarrhea, dizziness) or MBI will be collected throughout the study.

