## Project originality and expected results

We propose a single-center, mixed-methods pilot study to assess the acceptability and usability of the eMind application in a population of smokers wishing to quit.

eMind is the first Mindfulness application for smoking cessation to enable patients to follow a complete 8-week MBI that recreates as closely as possible the conditions of a classic MBI. It differs from other Mindfulness applications in that most existing applications offer only elements of Mindfulness programs, without the rich, intensive and progressive training process of a standard 8-week program. Compared with a traditional face-to-face program, Mindfulness practice via eMind is said to encourage patients' autonomy in deciding when to practice, and to be more compatible with their life rhythms.

The eMind application will be co-constructed: it will be based on a partnership research approach with patient participation. A first version of the content has been created in the university hospital addictology department by healthcare professionals trained in mindfulness. This first version of the application - a beta version - will be modified according to patient feedback. To reward their contribution to the final version of the application, patients will be compensated in the form of a gift card. A session to present the results of the study and the new version of eMind will be organized once the modifications have been taken into account.

Knowledge of the acceptability and usability of the beta version of eMind, as well as a study of the motivations and obstacles to its use, will provide us with information on the needs of the participants in terms of the operation of the eMind application. This will make it easier to overcome any obstacles encountered, so as to achieve optimum involvement. These evaluations will enable us to make the necessary adjustments before rolling out the program on a larger scale.

Data on the effect size of our intervention will be used to calibrate a large-scale national intervention trial aimed at evaluating the effectiveness of the improved version of eMind, thanks to feedback from participants in the HowToMind study, as part of the participatory research approach.

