# METHODOLOGY

## Study diagram

We propose a single-center pilot study to characterize the acceptability and usability of the beta version of the eMind application among smokers. The effect size of this intervention on the maintenance of smoking abstinence will be collected as a secondary endpoint.

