## End of study

Telephone call 6 months after inclusion, during which the following information will be collected:

- Tobacco consumption at 6 months
- A compendium of mindfulness practice

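### The 7-day abstinence definition carries no CO criterion, although exhaled CO is measured at the same week 4, 8 and 12 visits

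*Protocol*

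**What the plan says.** Protocol section 3.2 (Secondary endpoints), repeated in the synopsis, gives the definition: "Smoking abstinence will be defined as the absence of tobacco consumption for 7 days prior to the assessment visit". The sentence before it sets the CO schedule: "A CO test will be performed at inclusion, 4 weeks, 8 weeks and 12 weeks". The visit lists in section 6.4 and the chart in section 6.11.2 repeat CO at the three follow-up visits.

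Up to week 12, tobacco consumption "will be measured using an electronic consumption calendar implemented in our application". Section 6.7 makes this calendar a daily entry by the patient.

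The last contact is different in kind. Section 3.2 lists "Assessment of tobacco consumption at 6 months, during a telephone call", and section 6.5 confirms that it is a call. No CO is scheduled for it, and no 7-day window is stated.

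On the use of the result, section 4.1 says: "The effect size of this intervention on the maintenance of smoking abstinence will be collected as a secondary endpoint". Section 1.3, like the synopsis, adds: "Data on the effect size of our intervention will be used to calibrate a large-scale national intervention trial".

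**The concern.** The definition rests on what the participant enters. An objective marker is taken at the same visits, but nothing in the protocol connects it to the classification. A zero-smoking calendar with a raised CO therefore yields an abstinent participant.

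The setting makes over-reporting plausible. The study has one arm and no comparator. Staff of the department where the visits take place created the app content (section 1.1.4). The principal investigator is alerted when the calendar is left empty (section 5.1), so participants report to people with an interest in the result. Over-reporting would push abstinence upward, and the definition has nothing to correct it.

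What is at stake is not a decision within this pilot but a figure that may be taken into the planning of the next trial.

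**Working it through.** The protocol states no calculated figure for abstinence, and N = 60 is set by convention (section 4.2.1), so there is nothing to reproduce. The check is mainly textual, followed by one illustration of size.

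**1. Text set side by side**

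- Definition (3.2 and synopsis): no tobacco for 7 days before the visit, and no CO condition.
- Source of consumption to week 12 (3.2, 5.1, 6.7): patient-completed app calendar.
- CO (3.2, 6.4, 6.11.2, 7.3): measured at inclusion and weeks 4, 8 and 12. None of these places gives a cut-off, links CO to abstinence, or says what happens when report and CO disagree.
- Reason given for the definition (3.2): 7-day rather than continuous abstinence, because of recall bias and missing data. No reason is given for leaving CO out.
- 6 months (3.2, 6.5): telephone only, so the definition, which is tied to a visit, does not directly apply and CO cannot be taken.

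The definition is therefore complete as stated and excludes CO by its wording.

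**2. Illustration of size**

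Inputs: n = 60 (section 4.2.1). The 15 reported abstainers are an assumption, giving 15/60 = 25%. The share f of reported abstainers who would fail CO is also an assumption, taken as 10% to 25%, because the documents give none.

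Verified rate = reported rate × (1 − f):

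- f = 10%: 25% × 0.90 = 22.5%
- f = 20%: 25% × 0.80 = 20.0%, or 12/60
- f = 25%: 25% × 0.75 = 18.75%

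The shift is 2.5 to 6.25 percentage points.

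Exact (Clopper-Pearson) 95% interval for x of n: lower limit = 2.5th percentile of Beta(x, n − x + 1); upper limit = 97.5th percentile of Beta(x + 1, n − x).

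- 15/60: Beta(15, 46) and Beta(16, 45) give 14.7% to 37.9%.
- 12/60: Beta(12, 49) and Beta(13, 48) give 10.8% to 32.3%.

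The whole illustrated range, 18.8% to 22.5%, lies inside the first interval. The shift is smaller than the sampling uncertainty at this sample size, but it acts in one direction and a larger sample would not remove it.

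**The case against.** The strongest reply is that the protocol never says CO will be ignored. CO appears under secondary endpoints, directly before the definition, and a cut-off and the handling of discordant results could be set in an SAP that is not available here. Part of this stands: it would be wrong to say that CO enters no endpoint, since it may well be summarised descriptively. But the abstinence definition itself is stated in full. An SAP that added CO would be changing that definition, not supplying a missing detail.

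Several stronger readings are tempting, and the documents do not support them.

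- *That abstinence is the main smoking outcome.* The primary endpoint is regularity of use and the MARS-F score (section 3.1). Abstinence is one of several secondary endpoints, analysed descriptively or exploratorily and without tests (sections 10.1 and 10.3).
- *That over-reporting would remove most of the gap between the 16% and 25% in section 1.3.* Those are 1-year rates in a public-health illustration, not outcomes of this study. There is also no reason to lower one and leave the other. With an assumed two-sided 5% level and 80% power, 16% against 25% needs 315 per arm. Lowering both by 10%, to 14.4% and 22.5%, needs 359. Lowering only the upper one to 22.5% needs 577, and the documents give no basis for that asymmetry.
- *That the 12-week and 6-month results will be read as one series.* Section 3.2 lists the 6-month item separately, as consumption by telephone.
- *That the next trial will be planned from this abstinence rate.* Sections 1.3 and 4.1 speak of an effect size and name neither a rate nor a time point. If the 6-month figure were used, a CO criterion at the visits would not verify it.

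**Conclusion.** The point holds as a modest, inexpensive improvement to a secondary endpoint. Section 3.2 defines abstinence without a CO criterion although CO is taken at the same week 4, 8 and 12 visits, so a report of no smoking with a raised CO is classed as abstinent.

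The size is not known. If 15/60 reported abstinence and 10% to 25% of them failed CO, the rate would fall from 25% to between 22.5% and 18.8%. Both the 15/60 and the failure share are assumptions. The primary endpoint, the sample size and the focus groups are unaffected. The relevance comes from the planned use of effect-size data for a national trial. The 6-month result remains unverified whatever is done at the visits.

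**What to change.** In section 3.2 and the synopsis:

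- At weeks 4, 8 and 12, define abstinence as no tobacco in the preceding 7 days together with exhaled CO below a cut-off. Write the cut-off into the protocol before outcome data are examined.
- State how a zero-smoking report with a raised CO, and one with no CO value, are classified. For example, count both as not verified abstinent and give the number of each.
- Report self-report-only abstinence next to the CO-verified rate, so that the difference between the two is visible to whoever plans the next trial.
- At the 6-month call, ask the same 7-day question and label the result self-reported, not CO-verified.

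No new measurement or visit is needed. The costs are slightly lower rates, some participants unclassifiable or counted as not verified because CO is missing, and possibly a protocol amendment. Section 11.3.1 records ethics approval, and section 11.3 requires a favourable opinion for substantial modifications, which a changed endpoint definition may be.
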